#### Secondary outcomes

Healthcare provider knowledge and current practices related to the HPV vaccine, measured by survey (yearly in Years 1–4). Provider perspectives regarding feasibility/acceptability and appropriateness of the intervention in the pediatric oncology setting, and provider adherence (fidelity) to intervention components, measured by survey (yearly in Years 1–4), and interview (once during intervention year [Year 2 or Year 3]).

#### Exploratory outcomes

Change in survivor HPV vaccine series completion rates, and ongoing HPV vaccine initiation rates in years subsequent to implementation of the intervention (sustainability), measured using state vaccine registry data accessed via the EMR at each participating site as part of the QI project associated with this research. The exploratory outcomes will be measured as of the final day of each relevant study year.

### Analytic plan

#### Effectiveness trial

Unless otherwise noted, all statistical tests will be two-sided. The main hypothesis of the intervention’s effect will be tested using a mixed effects logistic regression model including a random intercept for each site. The base model for HPV vaccine initiation for participant *i* at site* j* during year* y* without covariates will be:$$\mathrm{log}\left({Odds}_{initiation,i,j,y}\right)={\beta }_{0}+{\beta }_{1}\bullet {year}_{j,y}+{\beta }_{2}\bullet {x}_{intervention,j,y}+{b}_{j}$$

where $${year}_{i,j}$$ indicates the study-year of the visit, and $${x}_{intervention,j,y}$$ equals 0 if site *j* has not been exposed to the intervention by $${year}_{j,y}$$, and equals 1 if it has, and $${b}_{j}$$ is the random intercept for site *j*. The primary hypothesis will be tested by the significance of the coefficient $${\beta }_{2}$$ in the model, which will capture the initial year of active intervention. Exploratory aims include testing whether the intervention results in increased rates of series completion and whether there is a sustained intervention effect in increasing HPV vaccine initiation. The analysis for series completion will parallel the analysis for initiation, with the exception that the analytic cohort for each year will be limited to those who had not completed the series prior to their index clinic visit for that year. Sustained effects will be tested using a similar model augmented by specific coefficients for duration of time in the intervention arm:$$\mathrm{log}\left({Odds}_{initiation,i,j,y}\right)={\beta }_{0}+{\beta }_{1}\bullet {year}_{j,y}+{\beta }_{2}\bullet {x}_{intevention,j,y}+{\beta }_{3}\bullet {x}_{2int,j,y}+{\beta }_{4}\bullet {x}_{3int,j,y}+{b}_{j}$$

In this model, $${\beta }_{1}$$ will continue to account for a constant secular trend, while $${\beta }_{3}$$ will allow for an additional effect in the 2^nd^ year of intervention and $${\beta }_{4}$$ will similarly allow for an additional incremental effect in the third year. Thus, the log odds of initiation for a participant at site *j* in year 4 for a site in the third year of intervention will be estimated as $${\beta }_{0}+{\beta }_{1}\bullet 4+{\beta }_{2}+{\beta }_{3}+{\beta }_{4}$$ + $${b}_{j}$$. While hypothesis testing will be included in the exploratory aims, the focus will be on reporting estimated rates of outcomes and intervention effects with confidence intervals. For each outcome, secondary analyses will include patient age at visit, sex, insurance type, and race/ethnicity as covariates to improve the precision of estimates and provide an estimated standardized prevalence. We will also evaluate the impact of clinic level factors on vaccination initiation rates (e.g., clinic volume, provider characteristics, practice size, geographic location, and baseline initiation rates) as fixed effects. We will also report the HPV vaccine initiation rate among survivors who were vaccine-naïve at cohort entry (i.e., incidence of vaccine initiation). Last, we will perform subgroup analyses stratified by relevant biological variables (i.e., age at visit, sex, and race/ethnicity groups). For survivors who complete > 1 clinic visit/study year, the number and timing of subsequent clinic visits during the study period will be included as covariates in secondary analyses. Patients who develop a relapse or subsequent malignancy requiring active cancer treatment at any time during the study period will be removed from the data set as of the date of diagnosis of the relapse or subsequent malignancy. Parallel analyses will further consider providers as random effects within sites, adding a random intercept for each provider. Given the potential complexity of correlation structures and nesting, the main hypothesis tests will also be reported using permutation testing. As an example, for permutation testing the main effect based on coefficient $${\beta }_{2}$$, for multiple (> 1000) iterations, participants will be randomly assigned to sites and the models fit to develop an empirical distribution for estimates of $${\beta }_{2}$$ under the null hypothesis of not different. The p-value of $${\beta }_{2}$$ (with genuine assignments) will be estimated from distribution of coefficients estimated from the permutations.

*Sample Size and Power.* Based on a combination of our prior work [6], secular trends since publishing that work, and general population data regarding state-specific vaccination rates [53], pre-intervention prevalence rates of vaccine-initiated patients at the 6 sites are estimated to be 0.404, 0.496, 0.462, 0.473, 0.415, and 0.488, for an average prevalence rate of 0.456, with a stable baseline incidence initiation of 0.025 (or 2.5 absolute percentage points) [6, 53]. For evaluating the intervention, we expect to have approximately 1273 patients with clinic visits per year with site-specific numbers estimated as 227, 215, 135, 104, 403, and 189. Power was estimated using simulations making conservative assumptions about the number of available appointments, and rates of increase. From simulations, we have > 80% power to detect increased rates of initiation resulting in average prevalence after year 2 (1^st^ year of intervention) of 48.2% for the control practices vs. 57.0% for the intervention practices, an absolute difference of 8.7%, which is less than the 10% difference we expect to observe. In terms of the logistic regression model, this equates to a 6% relative increase per year in rates of incident initiation (for a secular trend with an absolute increase of 2.5%) in the control group and a 24.3% relative increase in the intervention group. Subgroup analyses: For a subgroup of half our sample (e.g., stratifying by sex, age at visit, or race/ethnicity) we have 80% power to detect a difference in rates of 49% vs. 61%.

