### Randomization

In this stepped-wedge cluster-randomized design, randomization will occur at the site level, with three sites randomized to begin the intervention in Year 2, and three sites randomized to begin the intervention in Year 3 (Fig. 3). There is no difference in the intervention between the two groups other than the intervention start date. The study’s stepped-wedge design incorporates a control period for all participating sites during Year 1, allowing for collection of baseline vaccination rates, thus avoiding historical comparisons. Before the beginning of Year 2, sites will be randomized according to the stepped-wedge design. The sites assigned to the control condition in Year 2 (sites A, B, C) will be assigned to the intervention in Year 3, and the Year 2 intervention sites (sites D, E, F) will be moved to the post-intervention (sustainability) condition for Year 3. All sites will be assigned to the post-intervention (sustainability) condition for Year 4. The stepped wedge design will allow comparison of the primary outcome (HPV vaccine initiation rate; i.e., proportion of survivors in targeted population who have received ≥ 1 HPV vaccine dose, as of the last day of each study year) across groups (control vs. intervention), while allowing each site to serve as its own pre-intervention control, and using the control observations in Years 1 (all sites) and 2 (sites A, B, C) to estimate secular trends. Sustainability will be assessed in the post-implementation period, i.e., in Years 3 (sites D, E, F) and 4 (all sites) (Fig. 4).

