Upon adding each survivor to the study roster, the CRA will access the state vaccine registry and abstract all HPV vaccine dose(s) and associated date(s) of administration occurring prior to the date of the survivor’s cohort entry visit. At least yearly throughout the data collection period (Years 1–4), the CRA will access the state vaccine registry and abstract any additional HPV vaccine dose(s) and associated date(s) of administration occurring since the most recent data abstraction. Additionally, dose(s) and date(s) of additional vaccines recommended for adolescents (i.e., meningococcal, Tdap, influenza and COVID-19), will be abstracted by the CRAs at the same timepoints, for use as co-variates in the analysis, as it is important to understand whether uptake of the HPV vaccine differs from uptake of the other recommended adolescent vaccines [52]. All data will be completely de-identified prior to submission to the study coordinating center; survivors with visits in more than one year will be linked so that multiple observations per survivor can be addressed in the analysis. Coded roster data (with no elements of personal health information [PHI]) will be submitted weekly by participating sites to the study coordinating center via the study’s REDCap® study database. Data quality will be monitored in real-time by the site CRAs for each individual site and by the CRA at the study coordinating center for the overall study, using the study Standardized Operating Procedures, which include detailed instructions for data collection, verification, and cleaning. Additionally, range checks for key variables, and warnings to prevent missing data, are built into the REDCap® study database.

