#### Implementation trial

*Quantitative analysis.* Descriptive statistics (e.g., frequency, percentage mean, standard deviation [SD], median, range) will be used to summarize quantitative measures. Scores for Provider HPV Vaccine-related Knowledge/Practices will be modeled at the provider level using mixed models similarly to the methods for the Effectiveness Trial, to properly account for repeated observations and within-practice clustering, but with a continuous rather than binary outcome. Model-based predictions with confidence intervals will be reported over time and by intervention exposure, and will be displayed graphically. We expect to be underpowered for formal hypothesis testing, but model-based effect estimates for HPV-related Knowledge and Practices will be reported. *Sample Size and Power.* We recognize that we may not have sufficient power to test objective measures of provider HPV vaccine-related knowledge and practices, or objective ratings of the intervention; as such, the Implementation Trial is a secondary aim, and the provider knowledge/practices portion of the analysis will be exploratory.

*Qualitative analysis.* We will code interview transcripts and analyze them using content analysis. Two investigators will evaluate each transcript using line-by-line open coding to develop a preliminary codebook of emerging themes. We will use the preliminary codebook to guide additional analyses, and will develop a robust codebook as additional transcripts are analyzed. We will use team discussions to arrive at a consensus regarding final coding, aggregate the codes, and categorize them to identify major themes. Data saturation will occur when no new themes emerge. Qualitative software (e.g., NVivo) will be used for analysis.

*Mixed methods: Integration of data*. Results from the quantitative and qualitative analyses will be integrated through comparison to generate metainferences regarding the feasibility/acceptability of the intervention. The analysis will be weighted toward the qualitative strand [54]. The mixed analysis will expand our understanding of providers’ experiences implementing the intervention.

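### The standard error of the primary intervention effect ignores repeated yearly records of the same survivor; taken alone, this makes it too large

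*Protocol article*

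**What the plan says.** In the Analytic plan (Effectiveness trial), the main hypothesis is to be "tested using a mixed effects logistic regression model including a random intercept for each site". The printed equation contains an intercept, a linear year term, an intervention indicator and the site intercept. Participants are indexed, but no term belongs to a participant. "The primary hypothesis will be tested by the significance of the coefficient" β2. "Unless otherwise noted, all statistical tests will be two-sided".

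The Randomization section defines the outcome as the share of the target population with at least one dose, "as of the last day of each study year". The series-completion analysis parallels the initiation analysis, "with the exception that the analytic cohort for each year will be limited to those who had not completed the series" by that year's index visit. That restriction is an exception for completion, so the initiation analysis keeps survivors who are already vaccinated.

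Three other statements bear on repeats:
- Patient-level data: "survivors with visits in more than one year will be linked so that multiple observations per survivor can be addressed in the analysis".
- Implementation trial: provider scores will be modelled much as in the effectiveness analysis, "to properly account for repeated observations and within-practice clustering".
- Effectiveness trial: "Parallel analyses will further consider providers as random effects within sites, adding a random intercept for each provider". This extra level is the provider, not the survivor.

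The Effectiveness trial section also adds a permutation test of β2, motivated by complex correlation, in which participants are reassigned at random among sites.

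**The concern.** A survivor who has had one dose is a 1 in every later study year, and one who has had none usually stays 0. Successive records of a survivor are therefore almost copies of each other. The primary model treats them as independent given site, which contradicts the intent stated under Patient-level data.

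β2 is read largely from change within sites. When the same people are seen before and after, that change is known more precisely than independent samples would allow, and the model cannot see this. At stake are the standard error, confidence interval and p-value of the primary result, and the match between the power simulation and the analysis.

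**Working it through.** **Inputs from the Protocol article (Sample Size and Power).** Site sizes are 227, 215, 135, 104, 403 and 189 (total 1273 a year). Baseline prevalences are 0.404, 0.496, 0.462, 0.473, 0.415 and 0.488 (mean 0.456). The secular rise is 2.5 points a year. The detectable contrast is 48.2% vs 57.0%, with power above 80%.

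**Assumptions.** The share q of survivors seen again the next year is not given; 0, 0.5 and 0.8 are used. The Background says only that survivors return regularly. The nine-year age band (9-17) removes roughly one in nine a year by ageing out, so 0.8 is possible. Two-sided alpha is taken as 0.05.

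**The plan's own figure.** A two-proportion calculation with 636 per arm, 0.482 vs 0.570, gives 88.2% power. Simulating the plan's model with no repeats and an 8.75-point effect gives 66.7% (Years 1-2), 68.0% (Years 1-3 without sustainability cells) and 88.8% (Years 1-4). Power above 80% is attainable, but it cannot be matched exactly because the overlap and data window are not stated.

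**Direction, by hand.** Take two years with prevalence p1 = 0.456 and p2 = 0.456 + 0.025 = 0.481. For a returning survivor, status 1 in year 1 implies 1 in year 2, so the covariance is p1(1 − p2) = 0.456 × 0.519 = 0.2367. The correlation is 0.2367 / √(0.456 × 0.544 × 0.481 × 0.519) = 0.2367 / 0.2489 = 0.95. The variance of a within-site change shrinks by about 1 − 0.95q, so model SE over true SD is about 1/√(1 − 0.95q):
- q = 0.5: 1/√0.525 = 1.38
- q = 0.8: 1/√0.24 = 2.04

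**Simulation, site effects left essentially unpenalised** (this isolates the within-survivor effect), no intervention effect, Years 1-4:

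| q | True SD of β2 | Model SE | Ratio | Rejection, model SE | Survivor-clustered SE | Rejection, clustered |
|---|---|---|---|---|---|---|
| 0 | 0.110 | 0.110 | 1.00 | 5.1% | 0.110 | 5.1% |
| 0.5 | 0.081 | 0.110 | 1.36 | 0.6% | 0.082 | 4.6% |
| 0.8 | 0.056 | 0.110 | 1.96 | 0.0% | 0.055 | 5.4% |

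With no repeats the model SE is right, so the repeats cause the discrepancy. For Years 1-2 at q = 0.8 the figures are 0.163 against 0.079 (ratio 2.06), close to the hand value.

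**Simulation, the plan's model with its site random intercept,** no effect, q = 0.8:
- Years 1-2: model SE 0.140, true SD 0.112, ratio 1.25, rejection 3.2%.
- Years 1-4: model SE 0.108, true SD 0.058, ratio 1.86, rejection 0.0%. At q = 0.5 the figures are 0.108 and 0.085, ratio 1.27.

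The milder Years 1-2 figure is partly an offset. With six sites and no repeats, the random-intercept test in that window already rejects 11.8% under the null.

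**Cost in power** at the 8.75-point effect, unpenalised site effects, q = 0.8. Years 1-2: 64% with the model SE, 98% with the survivor-clustered SE. Years 1-4: 97.9% and 99.9%.

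**Site-by-year variation.** Assume a site-by-year SD of 2 points, q = 0.8, Years 1-4, unpenalised site effects. The true SD rises to 0.071. The survivor-clustered SE stays at 0.055 and rejects 12.8%; the model SE of 0.110 rejects 0.2%. Correcting for survivors alone would make the test anti-conservative.

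**The case against.** **The permutation test already deals with it.** This is the strongest reply. The unit shuffled is the participant. If each survivor's linked years move together, the null distribution keeps the correlation: over four years at q = 0.8 the permutation SD was 0.058 against a true SD of 0.059, and at q = 0.5 it was 0.075 against 0.080. This stands in part. It would be wrong to infer that the plan has nothing to offer on repeats. But the article does not say that a survivor's years stay together, the test is an additional report, and it leaves the SE and interval of β2 unchanged. Reassigning participants rather than the randomised sites is also open to question on other grounds.

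**The error is conservative and the stated power survives.** A reader might infer that ignored repeats produce false positives. The calculations show the opposite for this source. A reader might also infer that the power claim fails because of it. Over four years, power with the model SE is 94% to 99% at q = 0.5 to 0.8, so the claim holds in that window. The Years 1-2 shortfall is present with no repeats at all (66.7%).

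**The article condenses a fuller plan.** The equation is labelled a base model without covariates, and a variance estimator is often left to an analysis plan. This would answer a complaint of missing detail. It does not answer this point: the random structure and the primary test are both written out, and followed as written they give a miscalibrated SE.

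**Conclusion.** The concern holds for the Wald SE, interval and p-value of β2. Under assumed year-to-year recurrence of 50% to 80%, the omission taken alone inflates the SE about 1.3 to 2 times over Years 1-4. It inflates it about 1.25 times for the Years 1-2 contrast at 80% with the site random intercept. The article says that β2 captures the first intervention year, so the smaller figure matters as much as the larger.

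Two stronger conclusions are not supported. The first is that the trial's reported intervals will certainly be too wide: that is the effect of this error alone, while the omitted site-by-year variation and the small number of sites push the other way, and the net result cannot be fixed from the document. The second is that the outcome should be changed to initiation among unvaccinated survivors. The article defines the primary outcome as a prevalence and already plans to report initiation among those vaccine-naïve at cohort entry.

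The sizes rest on the assumed recurrence, the article's planning prevalences and an alpha of 0.05. The direction follows from an outcome that cannot reverse and an effect read mainly within sites.

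**What to change.** Keep the prevalence outcome and make three changes.

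1. **Effectiveness trial, primary model.** State that the SE and interval of β2 account for repeated records of the same survivor, by survivor-level clustered variance or a bootstrap using the linked IDs. Add a site-by-year term in the same step. The final variance must contain both components; resampling survivors within sites reproduces only the first.
2. **Effectiveness trial, permutation test.** State that all years of a survivor move together.
3. **Sample Size and Power.** Use the same structure in the simulation, and state the assumed recurrence and the study years used.

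A model restricted to survivors still vaccine-naïve at that year's index visit can be a supporting analysis. It should not replace the primary outcome, because it estimates incidence rather than prevalence.

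The cost is plan wording and modest extra analysis. No new data are needed, since the linked identifiers are already collected. Intervals may narrow or widen, depending on how much sites vary from year to year.

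### The exploratory series-completion model omits HPV doses already held at the index visit, so its odds ratio sits nearer the null than the dose-conditional one and power is lower

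*Protocol article*

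**What the plan says.** The Analytic plan (Effectiveness trial) defines a logistic model for initiation with a linear year term, an intervention indicator and a random site intercept. For completion it states that "The analysis for series completion will parallel the analysis for initiation", except that each year's cohort is "limited to those who had not completed the series prior to their index clinic visit for that year". No other change to the model is given.

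For every outcome, the same section says that "secondary analyses will include patient age at visit, sex, insurance type, and race/ethnicity as covariates to improve the precision of estimates". It also adds the number and timing of further visits. The Patient-level data section names other adolescent vaccines as covariates. HPV doses held at the index visit are not listed as a covariate, stratum or subgroup for completion.

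The data are available: on roster entry the site research assistant will "abstract all HPV vaccine dose(s) and associated date(s) of administration occurring prior to the date" of cohort entry, and later doses are added at least yearly. The plan does separate survivors by dose status for initiation: "We will also report the HPV vaccine initiation rate among survivors who were vaccine-naïve at cohort entry". It has no counterpart for completion.

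**The concern.** The completion cohort holds two groups with very different prospects. A survivor with no dose must receive the whole series by the last day of the study year, while one who has started needs only what remains. Dose status at the index visit is in effect the baseline value of this outcome, and is probably its strongest predictor. The plan must already know it to decide who is in the cohort.

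In a logistic model, leaving out a strong predictor does not leave the treatment odds ratio unchanged. It gives a marginal odds ratio closer to 1 than the one within dose groups, and usually a weaker test. A completion effect in six clinics is hard enough to detect without that loss. There is also a narrower risk: if the share of already-started survivors shifted between site-years in step with rollout, beyond chance, the unadjusted coefficient would take up the shift.

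**Working it through.** **Inputs from the Protocol article (Sample Size and Power).** Site sizes 227, 215, 135, 104, 403 and 189 (total 1273 per year); mean initiation prevalence 0.456; baseline initiation 2.5 absolute points per year. Tests are two-sided; a 5% level is assumed. The plan states no power for completion, so there is no figure to reproduce.

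**Assumed, because the document gives no value.** Share of initiators already complete, c: 40% to 80%. Yearly control completion if unstarted / started (q0/q1): 2%/30%, 2%/45% or 5%/25%. Conditional odds ratio: 2.1. As a check on q0: if 2.5 points of all patients start each year, at most 0.025/0.544 = 4.6% of the unstarted can start, let alone finish, so 5% is already generous.

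**1. Started share of the cohort.** s = 0.456(1 − c)/(1 − 0.456c). For c = 40%, 60% and 80%, s = 33%, 25% and 14%. The steps below use 25%.

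**2. Attenuation of the odds ratio.** At 2%/30%:
- Control: 0.75×0.02 + 0.25×0.30 = 0.090, odds 0.0989.
- Intervention: multiplying the odds in each group by 2.1 gives 0.0411 and 0.4737; pooled 0.75×0.0411 + 0.25×0.4737 = 0.1492, odds 0.1754.
- Pooled odds ratio: 0.1754/0.0989 = 1.77.

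The same steps give 1.59 at 2%/45% and 1.94 at 5%/25%.

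**3. Standard error and power.** Simulating the control and first-intervention site-years, with site effects and linear year, gave the standard errors below. Power is approximated as Φ(log OR/SE − 1.96), with log 2.1 = 0.742 for the adjusted model.

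| q0/q1 | Unadjusted log OR, SE | Power | Adjusted SE | Power |
|---|---|---|---|---|
| 2%/30% | 0.573, 0.31 | 46% | 0.35 | 56% |
| 2%/45% | 0.466, 0.27 | 41% | 0.33 | 61% |
| 5%/25% | 0.664, 0.30 | 60% | 0.31 | 67% |

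The unadjusted standard error is the smaller one in every row; power falls because the estimate shrinks by more. Power counted directly in several simulation runs was 43–51% vs 60–62%, 41–46% vs 62–68%, and 56–62% vs 63–67%. At a conditional odds ratio of 1.8, with c at 40–70% and other completion rates (1–5% and 20–40%), the pooled odds ratio was 1.53–1.70 and power rose from 24–43% to 30–50%. These simulations left out within-survivor correlation, so absolute powers are optimistic.

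**4. Does chance variation in mix mislead?** At 2%/30% the binomial variance per survivor is p(1 − p) = 0.09×0.91 = 0.0819. It splits into a between-group part, s(1 − s)(q1 − q0)² = 0.1875×0.0784 = 0.0147, and a within-group part, 0.75×0.02×0.98 + 0.25×0.30×0.70 = 0.0672. The two sum to 0.0819, so the unadjusted model's variance already contains sampling variation in mix. In simulation with only binomial variation in mix and no effect, type I error was 4.4–5.2% over 1,500 runs (about 4–9% in a smaller set of 400).

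**5. Shifts beyond chance.** If the started share were 30% rather than 25% in the intervention site-years, with no effect in either group and completion of 1.5%/30%, the pooled rates would be 0.1005 and 0.0863, an odds ratio of 1.18 (1.10 at 5%/20%). Imposing extra site-by-year variation of SD 5 points raised unadjusted type I error to about 6–14%. With SD 10 points it was 11–27%. With the dose term it stayed at about 4–6%. No passage gives or rules out such variation.

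**6. Later years.** Take c = 55%, 30% of started survivors finishing in the year, and the plan's 57.0% vs 48.2% prevalence after Year 2. If no new starter finishes that year, the next started share is (0.2052×0.7 + 0.114)/(0.2576 + 0.430) = 37% at intervention sites and (0.2052×0.7 + 0.026)/(0.1696 + 0.518) = 25% at control sites, from 27% before. By then the mix is partly a result of the intervention.

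**The case against.** A reader might infer that the omission makes the completion estimate less precise. On the model's own scale that is not so: the unadjusted standard error is smaller, and the unadjusted odds ratio is a valid marginal effect. The difference in power goes with a difference in estimand.

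A reader might also infer that a chance imbalance in the started share among six sites can pass as an effect. The documents do not support that either. Ordinary sampling variation is inside the model's variance, and the site intercept and linear year term absorb stable site differences and common linear drift. At 2%/30% a 5-point difference moves one site-year's completion rate by 0.05×0.28 = 1.4 points, but that is not a movement of the intervention coefficient.

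Pooling also suits the intervention, since the Provider toolkit's action plan covers both starting and finishing the series. Completion is exploratory, with the emphasis on estimates and intervals; no power is claimed for it; and age at visit and other vaccines may stand in partly for dose status. A fuller analysis plan may add terms.

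All of this stands and keeps the point small. What remains is that the article does fix the completion model and does list covariates for each outcome, chosen for precision, without the one most directly tied to this outcome.

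**Conclusion.** The point holds as a modest improvement to an exploratory analysis. Leaving out dose status pulls the completion odds ratio toward the null relative to the conditional one (2.1 to about 1.6–1.9) and costs about 5 to 25 points of power in most assumed scenarios, less where the two groups differ least. It does not enlarge the log-odds standard error, and it does not make pooling wrong. Distortion or excess type I error would need site-by-year shifts in the started share that exceed chance and line up with rollout. The direction is consistent across the ranges tried; the size rests on completion rates by dose status and a share of initiators already complete, neither of which the document gives.

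**What to change.** In the Analytic plan, for the completion contrast between control and first-intervention years (Year 2 for sites D, E, F; Year 3 for sites A, B, C), add a fixed effect for HPV doses held at that year's index visit, 0 vs 1 or more. Report model-standardised completion rates overall and by that category. State that the term is not used in any completion analysis that includes later post-intervention years, where earlier intervention may have changed dose status.

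The cost is one covariate from data already abstracted. The odds ratio becomes conditional on dose status, so the standardised rates must accompany it, and later years need a separate version without the term.
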